## **15 INSURANCE**

Insurance for all patients enrolled in the study in Switzerland is covered by "Zurich-Versicherungs-Gesellschaft AG, [name]" (Policy no.: 1099).

Insurance for patients enrolled in Germany and Austria will be taken separately.

Any damage developed in relation to study participation is covered by this insurance. So as not to forfeit their insurance cover, the subjects themselves must strictly follow the instructions of the study personnel. Subjects must not be involved in any other medical treatment trial without permission of the principal investigator (regular treatment excluded). The investigator must also be informed instantly, in the event of health problems or other damages during or after the course of study treatment.

The investigator will allow delegates of the insurance company to have access to the source data/documents as necessary to clarify a case of damage related to study participation. All involved parties will keep the patient data strictly confidential. A copy of the insurance certificate will be placed in the Investigator's Site File.

## **16 STUDY REGISTRATION**

The study is registered in the international trial registry ClinicalTrials.gov NCT02076373 (clinicaltrials.gov).

### **PUBLICATION POLICY**

The trial protocol will be published e.g. in the journal 'Trials' after ethical approval by the PI [name], the co-investigator [name], the Sponsor [name], the trial mentor [name], the study nurse [name], and the specialist involved in MRI analyses, [name].

After the statistical analysis of this trial the sponsor will make every endeavour to publish the data in a medical journal.

The list of authors will include in all publications based on this trial data the local PI and one or two treating physicians of each contributing centre (depending on the number of recruited infants and the individual requirements of medical journals). Of each satellite centres, as described in chapter 10.7 and SOP-08 "Verlegung", if at least one study patient has been cared the local PI will be included in all publications based on this trial data.

The order is defined as follows: First, second, and last position are reserved for study PI, the co-investigator, and the sponsor ([name], [name], and [name], respectively), 2 investigators of each centre in order of number of infants included in the study.

It is planned to publish the secondary outcomes e.g. on cUS findings and on MRI separately and before the primary outcome is achieved. According to the individual contribution of specialists, especially of [name] regarding cUS and MRI, the first, second, or last position will be taken by the specialist.

With regard to publications, the principles of data protection must be observed for patient data as well as for data pertaining to participating physicians.

## 1 Background

EpoRepair is a randomized, double-blind, placebo-controlled, international multi-center study to investigate the effect of intravenously administered Recormon (recombinant erythropoietin, hereafter referred to as EPO) on the outcome of very preterm infants (born before 32 gestational weeks and/or 1500 g of birth weight) after intraventricular haemorrhage (grade II-IV, diagnosed by cranial ultrasound at a chronological age < 9 d). The aim is to evaluate whether EPO has the potential to ameliorate the neurodevelopmental sequelae of intraventricular haemorrhage. EPO as a verum is compared to NaCl 0.9 % as a placebo. Randomization was done 1:1, blockwise within each center (using a separate randomization list for each of the nine participating centers). The trial protocol was published by [[name] et al. \(2015\)](#).

## 2 Outcomes

### 2.1 Primary outcome

The primary efficacy outcome of this trial is the intelligence quotient assessed by the Kaufman Assessment Battery for Children (Kaufman-ABC, German version) at 5 years of age. Children with speaking problems at 5 years will be assessed by an alternative, non-verbal intelligence test, the Snijders-Oomen non-verbal intelligence test (SON-R 2.5-7, German version), and the result will be used instead of Kaufman-ABC.

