### 5.1 Primary Variable(s)

Intelligence quotient assessed by the Kaufman Assessment Battery for Children (Kaufman-ABC) (German version) at 5 years of age will be the primary efficacy outcome variable. Children with speaking problems at 5 years will be assessed by an alternative non-verbal intelligence test, the Snijders-Oomen non-verbal intelligence test (SON-R 2.5-7, German version).

Neurodevelopmental follow-up examinations of VLBW infants at 18-24 months using the Bayley Scales III of Infant Development (BSID-III) will be an intermediate variable. However, as 2 year outcome assessment is limited in predicting later cognitive functions, the 5 year outcome will be the main outcome variable.

The vast majority of children will remain on their 5-year IQ trajectory, and there is good agreement between classification of cognitive abilities at 5 and 11 years of age. In the retrospective analyses on neurodevelopmental outcome of VLBW infants after EPO, differences between EPO-treated infants and controls were at the borderline of significance at 2 years of age whereas cognitive scores diverged between EPO-treated children and controls at 3-4 years and did more so at 6-7 years of age.

Children will be classified as either being normal or having minor or major impairment according to the overall results of the tests as summarized in the table below. Children with intelligence incapable of measurement because of impairment severity will be assigned IQ scores below the lowest standard score of Kaufman-ABC and the SON-R 2.5-7.

Normal development: All of the following:

- Normal neurological evaluation, IQ > 84
- No neurodevelopmental deficits

Minor impairment: One or more of the following problems:

- Subnormal cognitive abilities (IQ, 70-84)
- Gross and fine motor activity deficits
- Disorders of language development
- Visual and auditory deficiencies
- Attention disorders
- Abnormal socioemotional development

Major impairment: One or more of the following problems:

- Cerebral palsy
- Intellectual disability (US mental retardation) with IQ < 70
- Blindness, deafness
- Intractable epilepsy

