### 4 Analysis data set

The **full analysis set (FAS)** will contain all children randomized to the trial whose parents gave informed consent, except one child who had to be excluded from the study after randomization due to severe genetic damage which was an exclusion criterion (another child was recruited instead).

Due to missing outcome measurements (and maybe explanatory variables) we will use multiple imputation to be able to analyze the complete FAS (see also Sections 5.1 and 8). In addition, we will do complete case analyses and optionally apply a special method to account for missing data due to death (sensitivity analysis S4 in Section 5.1).

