### 5.1 Primary analysis

The primary outcome, IQ measured by Kaufman-ABC (or SON-R), will be compared between treatment arms (EPO vs. Placebo) using a linear mixed-effects model with "treatment" as fixed explanatory factor and a random intercept per "center". This will result in an estimate (and 95 % CI) of the EPO treatment effect on IQ. The model assumptions will be checked by visual assessment of the residuals and log-transformation of the primary outcome may be considered in case of violations. We will use the R package lme4 ([Bates et al., 2015](#)) to fit the models and the R package lmerTest to derive p-values via the Satterthwaite approximation ([Kuznetsova et al., 2017](#)).

It has to be noted, that a comparison of IQ among survivors who performed an IQ test is prone to bias due to the large proportion of children who die before the age of 5 years and due to other losses to follow-up (20 % loss was expected in total, ca. 15 % of the newborn babies already died in hospital). The bias would be particularly high if the reasons for, or the frequency of, losses differed between trial arms (see e.g. [Altman, 2009](#)). Adhering to the method proposed in the protocol and its published version ([[name] et al., 2015](#)), we will use multiple imputation for the missing IQ values ([van Buuren and Groothuis-Oudshoorn, 2011](#)). We thereby assume that data are missing at random (MAR) and we treat missingness due to death in the same way as missingness due to other reasons. For more details see Section 8. The analysis will be performed on the FAS, in line with the intention-to-treat (ITT) principle.

The following sensitivity analyses will be done in addition to the "main primary analysis" just described:

- S1 Covariate adjusted analysis with birth weight of the child, severity of the intraventricular hemorrhage (Grade II, III or IV), steroid administration before birth, steroid administration after birth and Socio-Economic Score (SES) of the mother as additional explanatory variables compared to the main primary analysis.
- S2 Model described for the main primary analysis but performed on the complete cases in the FAS only (without multiple imputation, not in line with ITT)

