## 8 Handling of missing data and drop-outs

We will multiply impute missing outcome and covariate data due to death or loss to follow-up in the FAS. Multiple imputation will be performed by the R package mice ([van Buuren and Groothuis-Oudshoorn, 2011](#)), and will be applied separately at each stage of analysis (see Section 5). The imputation model will use all relevant baseline variables, the randomized treatment and outcome variables collected up to the time of analysis, potentially using correlations among outcomes for imputation in case the amount of missing data differs among outcomes. We will produce  $m=20$  imputations per missing value and analyze the 20 resulting complete data sets using Rubin's rules to pool the results.

While multiple imputation assumes missingness at random (MAR), missingness not at random can be investigated using the random indicator method proposed by [Jolani \(2012\)](#), mentioned also in [van Buuren \(2018\)](#). The latter will be used for sensitivity analysis S3.

In addition, a principal stratification approach suggested by [Hayden et al. \(2005\)](#) may be applied in order to estimate the "survivor average causal effect" (SACE), as proposed for sensitivity analysis S4.

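### The SAP does not carry over, or give a number for, the protocol's below-floor IQ score for children too impaired to be tested, so how the primary analysis treats them is unresolved

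*Combined protocol and SAP*

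**What the plan says.** Protocol 5.1 defines the primary variable in three parts: Kaufman-ABC for most children, SON-R for those with speaking problems, and a scoring rule for those who can take neither. The third part reads: "Children with intelligence incapable of measurement because of impairment severity will be assigned IQ scores below the lowest standard score" of the two tests. No number is attached.

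SAP 2.1 repeats the first two parts ("Children with speaking problems at 5 years will be assessed by an alternative, non-verbal intelligence test") and leaves out the third. No other SAP section brings it back, and SAP 9, which lists even slight changes from the protocol, does not mention it.

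On missing IQs the SAP says three things:

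- SAP 4: because outcome measurements will be missing, "we will use multiple imputation to be able to analyze the complete FAS".
- SAP 5.1: missing IQ values are imputed under missing at random (MAR), and "we treat missingness due to death in the same way as missingness due to other reasons".
- SAP 8: "We will multiply impute missing outcome and covariate data due to death or loss to follow-up in the FAS".

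SAP 5.1 also says that, after a visual check of residuals, "log-transformation of the primary outcome may be considered in case of violations".

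**The concern.** A child who attends at 5 years but cannot be tested has no measured IQ, and the reason is very low ability. Under Protocol 5.1 that child has an assigned score, so nothing is missing. Under SAP 2.1 alone the field is blank, and SAP 4 and 5.1 appear to send every blank in the full analysis set to MAR imputation. The imputed value is then predicted from children who could be tested.

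These are the lowest values in the primary endpoint, in a trial of whether EPO reduces the sequelae of haemorrhage. If the untestable share differs between arms, the handling rule moves the estimate. It can understate a benefit, or make a null result look like a benefit. The protocol rule does not settle the matter, because a linear model of IQ needs a number and none is given.

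**Working it through.** **The plan's own figure.** Protocol 12.5 uses a difference of 10, SD 15, power 0.8 and two-sided alpha 0.05. Per arm, n = 2 × (1.96 + 0.84)² × 15² / 10² = 35.3, rounded up to 36, so 72 in total, as stated. Ten IQ points is therefore the yardstick.

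**Assumptions (none are in the documents).** Testable means are 85 on placebo and 89 on EPO, a 4-point effect. The assigned score F is 40, with a range of 30 to 50. The untestable shares are pP on placebo and pE on EPO. Death and loss are taken as unrelated to IQ, to isolate this one issue.

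**Scoring at F.** Each arm mean is (1 − p) × testable mean + p × F. The difference is therefore 4 + pP × (85 − F) − pE × (89 − F). With F = 40 this is 4 + 45 pP − 49 pE.

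**Imputing from treatment alone under MAR.** Untestable children receive the testable mean of their arm, so the difference stays at 4.0 whatever the shares.

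| Untestable, placebo / EPO | Scored at 40 | Imputed | Scored at 30 to 50 |
|---|---|---|---|
| 12% / 4% | 4 + 5.40 − 1.96 = 7.4 | 4.0 | 8.2 to 6.6 |
| 8% / 4% | 4 + 3.60 − 1.96 = 5.6 | 4.0 | 6.0 to 5.2 |
| 5% / 5% | 4 + 2.25 − 2.45 = 3.8 | 4.0 | 3.8 |
| 4% / 12% | 4 + 1.80 − 5.88 = −0.1 | 4.0 | −0.9 to 0.7 |

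The last column shows that the result also depends on the number chosen.

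**Adding an earlier outcome to the imputation model.** Suppose one 2-year score has correlation r with IQ among testable children, the same arm means and SD as IQ, and mean Z among untestable children. The imputed difference becomes 4 + r × [pP × (85 − Z) − pE × (89 − Z)].

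- 12% / 4%, r = 0.5, Z = 60: 4 + 0.5 × (3.00 − 1.16) = 4.9.
- 12% / 4%, r = 0.8, Z = 50: 4 + 0.8 × (4.20 − 1.56) = 6.1.

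Against 7.4, the gap falls from 3.4 points to between 1.3 and 2.5. For 4% / 12% the same settings give 2.8 and 1.4 against −0.1.

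**Cost in variance.** Take the planning case with testable means 80 and 90, SD 15, a score of 39 and 5% untestable in each arm.

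- Difference: 10 + 0.05 × 41 − 0.05 × 51 = 9.5.
- Variance per arm: 0.95 × 225 + 0.0475 × (mean − 39)², which is 293.6 and 337.3. The pooled SD is 17.8.
- Power at 40 per arm: 9.5 / (17.8 × √(2/40)) = 2.39, and 2.39 − 1.96 = 0.43, so 0.67. The design case gives 0.85.

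**Log-transform (secondary).** Simulated skewness, raw then logged:

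- Mean 87, SD 15, 8% scored at 40: −0.58 then −1.28.
- Mean 85, SD 15, test floor 40, no floor scores: 0.04 then −0.50.
- Mean 67, SD 21 (the observational figures in Protocol 12.5), test floor 40, 5% scored one point below it: +0.39 then −0.18.

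The log makes left skew worse and can reduce right skew.

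**The case against.** The best defence is that nothing has been revoked. SAP 8 confines imputation to death and loss to follow-up, and a child who attends but cannot be tested is neither. SAP 9 calls the plan generally in line with the protocol. Protocol 12.2 itself names the endpoint in short form without the scoring rule, so a summary that omits the rule does not show that it was removed. This stands as far as it goes: a reader might infer that the SAP orders these IQs to be imputed, and the text does not say so. It does not resolve the matter, because SAP 4 and 5.1 are worded for all missing IQs, and the protocol rule cannot be run without a number.

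A reader might also infer that untestable children would be given average-looking IQs. SAP 8 does not support that. Its imputation model uses baseline variables and earlier outcomes, and by the 5-year stage these include Bayley scores, cerebral palsy and imaging. Predictions would usually be low, which narrows the bias but does not remove it.

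Nor would harm be wholly hidden. Such a child would count as non-normal in the binary and three-category developmental outcomes of SAP 2.2.1. The sensitivity analyses help less. S2 is equally undefined for these children. S3 addresses data not missing at random but is optional and not specific to them. S4 is optional and concerns death.

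Finally, a reader might infer that the SAP's log option makes the skew worse. The option is only permissive and names no direction of skew. The strong worsening arises only when floor scores are in the data, and with a mean near 67 and SD 21 the log reduces absolute skew.

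**Conclusion.** The concern holds as a gap and a conflict in the definition of the primary outcome. Protocol 5.1 has a rule for untestable children. The SAP neither repeats it nor records its omission, and its missing-data sections point in different directions. An analyst could score these children, impute them or exclude them.

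The size cannot be fixed from the documents, which give no untestable share, test floor or arm difference. On the illustrative figures, the choice between scoring and treatment-only imputation matters little when the shares are equal (0.2 points at 5% each). It is worth 3.4 points at 12% / 4% and 4.1 points the other way at 4% / 12%, against a planning effect of 10. A realistic imputation model would leave part of those gaps. None of these figures is an expected loss for this trial.

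The log-transform is a side issue. The reason to avoid it is that it replaces an IQ difference with a ratio and would accentuate any left skew that floor scores create.

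**What to change.** - **SAP 2.1:** restate the protocol rule with one fixed score below the floors of both tests, taken from the test manuals and set before any 5-year IQ is seen by arm.
- **SAP 8:** state that this score counts as observed and is not imputed. Record the reason whenever no test is done; the item list in Protocol 6.9 does not show such a field.
- **SAP 5.1:** keep the primary estimate on the IQ scale and remove the log option. Add a rank-based sensitivity analysis, because the mean difference depends on the chosen score and ranks do not.
- **SAP 9:** mention the clarification.

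The cost is SAP wording, one data item and a little more analysis. The real downside is variance. With 5% floor scores in each arm, the illustration raises the SD from 15 to 17.8 and lowers power at 40 per arm from 0.85 to 0.67. The protocol's rule already implied that loss, but its sample size did not allow for it.

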### 2.2 Secondary outcomes

Secondary outcomes are grouped by the follow-up time at/up to which they are measured.

#### 2.2.1 Secondary outcomes at 5 years (like primary outcome)

- Normal overall developmental outcome (binary). Normal development at 5 years is defined as the combination of normal neurological evaluation, IQ > 84, and no neurodevelopmental deficits (all three conditions must be met).
- Mortality (binary)
- Developmental outcome categorized as normal, non-normal or dead (multinomial or binary: normal vs. non-normal or dead), combining the two outcomes just above into one

#### 2.2.2 Secondary outcomes at 2 years

- Bayley Scales III of Infant Development (BSID-III), combined score (continuous outcome, norm value 100, range ca. 30–150)

---

This outcome was neither prespecified in the study protocol nor in the published study protocol. It was added to take into account the considerable proportion of children who die before the age of 5 years.

- Subscore for motion (continuous, norm value 100)
- Subscore for cognition (continuous, norm value 100)
- Presence of impairment of motor function (cerebral palsy, binary)
- Presence of impairment of neurosensory function (blindness or deafness, binary)
- Mortality (binary)

### 2.2.3 Secondary outcomes up to term equivalent age

These outcomes are measured at slightly different times, some at 40 weeks postmenstrual age (PMA), some at 36 weeks PMA and some at 28 days of life (DOL).

#### Outcomes from advanced MRI at 40 weeks PMA

- Global brain abnormality score according to [Kidokoro et al. \(2013\)](#) (continuous from 0–40 and binary normal/mild vs. moderate/severe)
  - Subscore for white matter abnormality scale (continuous from 0–17 and binary: normal/mild vs moderate/severe)
  - Subscore for cortical grey matter abnormality scale (0–9), binary: normal/mild vs moderate/severe)
  - Subscore for deep grey matter abnormality scale (0–7), binary: normal/mild vs moderate/severe)
  - Subscore for cerebellar abnormality scale (0–7), binary: normal/mild vs moderate/severe)

#### Outcomes from cerebral ultrasound (cUS) until discharge (28 DOL and 36 weeks PMA)

- Brain injury grading (normal, moderately abnormal, severe brain injury, binary as normal/moderate vs severe, or normal vs moderate/severe)
- Posthaemorrhagic hydrocephalus (Grade 0–3, binary as  $\leq 1$  vs  $> 1$ )
- Composite cUS score at 36 weeks PMA, according to [Skiöld et al. \(2019\)](#) (continuous from 0–55 and binary: normal/mild vs moderate/severe)

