- Chorioamnionitis clinical just prior to delivery, present or absent (Clinical chorioamnionitis is diagnosed in women who had three or more of the following signs: leukocytes >20,000/ $\mu$ l, C-reactive protein (CRP) >40 mg/dl, temperature >38°C, maternal tachycardia >100 bpm, fetal tachycardia >160 bpm.)
- EPH-Gestosis (Preeclampsia, PE), present or absent (PE is defined as hypertension ( $\geq$ 140 mm Hg systolic and  $\geq$ 90 mm Hg diastolic blood pressure) and significant proteinuria  $\geq$ 300 mg/24h, or  $\geq$  ++ in urine dipsticks.)
- Mode of delivery, indicate if vaginal spontaneous, vaginal instrumental, caesarean section elective or secondary
- Umbilical artery pH
- Apgar score at 5, and 10 minutes
- Crib score, including lowest FiO2, highest FiO2, and worst base deficit, all before 12 hours of life
- Weight (g) and SD from mean weight at birth
- Head circumference (cm) and SD from mean length at birth
- Length (cm), SD from mean length at birth
- First Hct in % and first Hb in g/dl on admission at NICU
- EPO medication:
  - First EPO dose in ml, date and time of application, (T1)
  - Second EPO dose in ml, date and time of application, (T2)
  - Third EPO dose in ml, date and time of application, (T3)

- Fourth EPO dose in ml, date and time of application, (T10)
- Fifth EPO dose in ml, date and time of application, (T17)

- Weight (g) and SD from mean weight at DOL 28
- Head circumference (cm) and SD from mean length at DOL 28
- Length (cm), SD from mean length at DOL 28
- Hct in % and Hb in g/dl at DOL 28
- Complete cUS findings at DOL 1-4 and DOL 28
- 

cUS at DOL 28, graded in normal, moderately abnormal and severely abnormal brain injury

Comment: Findings of cUS will be graded in normal, moderately abnormal and severely abnormal brain injury, see below. This grading is a standard procedure in all neonatology units with small variations. cUS is a secondary outcome measure and performed in visit 0, visit 2, and visit 3. To unify grading it is defined below. In addition, correct grading will be supervised by the involved study staff.

Definition of normal, moderately abnormal and severely abnormal brain injury by cUS is as follows:

- Normal brain
  1. No cysts
  2. No ventricular dilatation
  3. No thinning of corpus callosum
  4. No enlargement of extracerebral spaces
  5. Normal cortical grey matter
- Moderately abnormal brain
  1. PVL grade 1 with either homogeneous or inhomogenous increased echogenicity

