## **12 STATISTICS**

### **12.1 Statistical and Analytical Plans**

There is presently no established medical therapy to ameliorate the neurological sequelae of IVH in VLBW infants. The beneficial effects of EPO must be considered hypothetical (based on retrospective analyses) until confirmed or refuted by a RCT. Our trial will be a multicentre, placebo-controlled, prospective, randomised, double-blind (verum:placebo = 1:1) clinical study. 8 centres in Switzerland, 3 in Germany, and 1 in Austria participate in the study. The study will include female and male VLBW infants with IVH (grade II-IV) diagnosed by cUS at a chronological age < 8 d (more than 96% of all cases of IVH occur within the first 5 d of life). The primary endpoint is the IQ of the children at age of 5 years (continuous outcome) and in addition the binary endpoint normal development. Moreover, 4 secondary endpoints are planned: MRI outcome, cUS outcome, BSID-III, and drug safety (including mortality), – the first 3 outcomes have ordinal and continuous measures and the last outcome is binary. Based upon these design considerations, the study will be analyzed using t-tests, linear and logistic regression.

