#### **Secondary endpoints:**

Normal overall developmental outcome at age of 5 years will be a secondary end point (binary variable). Normal development is determined in a neurological assessment at 5 years of age, including intelligence quotient (K-ABC or SON-R). Normal development at 5 years is defined as the composite outcome of: Normal neurological evaluation, IQ > 84, and no neurodevelopmental deficits.

Other secondary endpoints:

Advanced MRI at 40 weeks postmenstrual age (continuous outcome)

cUS at DOL 28 and at PMA 36 weeks (ordinal and continuous outcome)

BSID-III at two years of age (continuous outcome)

Mortality (binary outcome)

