#### **Hypotheses:**

The alternative hypothesis for all endpoints is improvement with regard to the endpoint in the group of EPO-treatment. The null hypothesis for all endpoints is no improvement with regard to the endpoint in the group of EPO-treatment compared to the control group.

The study hypotheses are one-sided – however, the tests will be performed 2-sided yielding corresponding confidence intervals and accordingly information about the direction of a potential difference between control and treatment group.

The significance level alpha is 0.05.

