### 5.2.2 Analysis of secondary outcomes

Continuous secondary outcomes will be compared between treatment arms (EPO vs. Placebo) using a linear mixed-effects model with "treatment" as fixed explanatory factor and a random intercept per "center", like the primary outcome. We will report the resulting estimates of the EPO treatment effects together with 95 % confidence intervals and p-values (unadjusted and adjusted for multiple testing). The model assumptions will be checked by visual assessment of the residuals and either log-transformation of the outcome or the use of a generalized linear mixed-effects model (e.g. with Poisson error) may be considered in case of violations. For the outcome BSID-III at two years (combined score and subscores) we will add a sensitivity analysis to adjust for additional covariates, as specified as sensitivity analysis S1 for the primary outcome (Section 5.1). Moreover, the methods described for sensitivity analyses S3 and S4 may also be applied to continuous secondary outcomes.

Binary secondary outcomes will be compared between treatment arms (EPO vs. Placebo) using a generalized linear mixed-effects model with binomial error (referred to as logistic regression in the study protocol), again with "treatment" as fixed explanatory factor and a random intercept per "center". The resulting odds ratio (OR) estimates of the EPO treatment effect will be reported together with 95 % confidence intervals and p-values. Binary secondary outcomes from cUS (severe brain injury, posthaemorrhagic hydrocephalus grade  $> 1$ ) were measured three times: at baseline, 28 DOL and 36 weeks PMA. The measurement taken at baseline and the time of outcome measurement (28 DOL vs. 36 weeks PMA) will be used as additional fixed explanatory variables in the model. A random intercept per patient (nested in center) will be added to the model, to account for the non-independence of the repeated outcome measurements. In addition, we will assess the treatment  $\times$  time interaction. We will use the R package lme4 (Bates et al., 2015) to fit the models for binary outcomes and derive p-values using likelihood ratio tests.

Developmental outcome (normal, non-normal or dead) will be compared between treatment arms by a chi-squared test and will also be analyzed as binary outcome (normal vs. non-normal or dead) as described above.

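### SAP 2.2.3 gives the three-level ultrasound brain-injury grade, classed as ordinal in the protocol, two alternative binary cuts and no ordinal analysis, and SAP 9 does not record the change

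*Combined protocol and SAP*

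**What the plan says.** **Protocol.** Section 6.5 defines the grade: "Findings of cUS will be graded in normal, moderately abnormal and severely abnormal brain injury". Section 12.2 lists the secondary endpoint as "cUS at DOL 28 and at PMA 36 weeks (ordinal and continuous outcome"). Section 12.1 says of MRI, cUS, BSID-III and drug safety that "the first 3 outcomes have ordinal and continuous measures and the last outcome is binary", and then that "the study will be analyzed using t-tests, linear and logistic regression". Neither section names a test or model for ordered categories.

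**SAP 2.2.3.** The grade appears as "Brain injury grading (normal, moderately abnormal, severe brain injury, binary as normal/moderate vs severe, or normal vs moderate/severe"). Every other cUS and MRI outcome in 2.2.3 that is dichotomised has one cut.

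**SAP 5.2.2.** The repeated-measures model is introduced for "Binary secondary outcomes from cUS (severe brain injury, posthaemorrhagic hydrocephalus grade" above 1). It is a binomial mixed model in which "The measurement taken at baseline and the time of outcome measurement (28 DOL vs. 36 weeks PMA) will be used as additional fixed explanatory variables", with random intercepts for patient and centre. The section covers continuous and binary outcomes, and gives a chi-squared test for the three-category developmental outcome. It has nothing for the three-level cUS grade.

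**SAP 9.** Other cUS and MRI changes are listed as deviations. The move from an ordinal to a binary cUS grade is not.

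**The concern.** The two cuts define different outcomes. Whether a moderately abnormal infant counts as an event depends on which is used, and so do the event rate, the odds ratio and the p-value. Section 2.2.3 offers both, 5.2.2 refers to one, and nothing says that the other is dropped. It is also unclear whether the grade adds one or two p-values to the Holm family in SAP 5.

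The result will be seen early. SAP 5 puts outcomes up to term-equivalent age in stage 1, and the protocol's publication policy foresees publishing cUS findings before the primary outcome is available.

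Two things are at stake: the error rate if the cut is settled after the data are seen, and the information lost when three ordered grades become two.

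**Working it through.** **Figures in the plan.** The plan gives no power, grade distribution or odds ratio for cUS. Its own sample size is for IQ: 2 × (1.96 + 0.84)² × 15² / 10² = 35.3, so 36 per arm and 72 in total, as protocol 12.5 states. That says nothing about cUS.

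**Inputs from the documents.** Two-sided 5% level (protocol 12.2: "The significance level alpha is 0.05"); 1:1 allocation; 50 per arm, the protocol 12.5 target after early loss.

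**Assumed inputs.** Five control distributions (normal/moderate/severe); a common odds ratio of 2.5 in favour of EPO; one visit; no adjustment for baseline or centre.

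**One scenario by hand: control 20/40/40%.** Dividing the control odds by 2.5:
- Severe: 0.40 has odds 0.667; 0.667/2.5 = 0.267, so the EPO rate is 0.211.
- Moderate or severe: 0.80 has odds 4; 4/2.5 = 1.6, so the EPO rate is 0.615.
- The control event rate is therefore 40% under one cut and 80% under the other.

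Power of a two-proportion test = Φ[(difference − 1.96 × pooled SE) / unpooled SE]:
- Severe cut: (0.1895 − 1.96 × 0.0921) / 0.0901 = 0.10, power 54%.
- Normal cut: (0.1846 − 1.96 × 0.0910) / 0.0891 = 0.07, power 53%.

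Power of the ordinal (proportional-odds) test, Whitehead's formula: the mean grade proportions are 0.292, 0.403 and 0.305, with cubes summing to 0.119. The information is (100/12) × (1 − 0.119) = 7.34. Then √7.34 × ln 2.5 − 1.96 = 0.52, power 70%.

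**Simulation.** 200,000 trials per row, tie-corrected Wilcoxon test on three grades against a two-proportion test at each cut. The last column is the chance, with no treatment effect, that at least one cut is significant.

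| Control normal/moderate/severe | Ordinal | Severe cut | Normal cut | Either cut, no effect |
|---|---|---|---|---|
| 20/40/40 | 69% | 54% | 53% | 9.7% |
| 10/50/40 | 65% | 54% | 38% | 9.9% |
| 30/40/30 | 68% | 46% | 62% | 9.3% |
| 10/30/60 | 66% | 64% | 38% | 9.6% |
| 5/45/50 | 64% | 61% | 21% | 9.6% |

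Loss against the ordinal test, from unrounded values: 2.2 to 22.0 points for the severe cut, 6.7 to 42.7 for the normal cut. With the effect present, the two cuts disagree on significance in 37% to 51% of trials.

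**Sensitivity.** Over seven distributions, odds ratios from 1.5 to 3 and 50 or 60 per arm, Whitehead's formula gives losses of about 1 to 28 points (severe cut) and 2 to 46 points (normal cut).

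**Non-proportional case.** Control 10/40/50 against EPO 10/60/30, where the benefit lies wholly in moving infants from severe to moderate: ordinal 41%, severe cut about 54%. The advantage reverses.

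**The case against.** **The model section already points to one cut.** SAP 5.2.2 names severe brain injury and adjusts for the baseline measurement. Protocol 6.5 counts any IVH as at least moderately abnormal, and every enrolled infant has IVH grade II to IV. At baseline, normal versus not normal would be the same for everyone, so baseline adjustment works only for the severe cut. This stands: it makes severe versus not severe the natural binary choice. It does not remove the second cut from 2.2.3.

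**The protocol promised no ordinal test.** A reader might infer that the SAP abandons a pre-specified ordinal analysis. The documents do not support that. The protocol gives cUS a scale label, shared with MRI and BSID-III, and names only t-tests, linear and logistic regression. What the SAP drops is the outcome type.

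**The power loss may be small.** If most infants still show IVH-related findings at day 28 and 36 weeks, few are normal and the ordinal test moves towards the severe cut. In the three rows with 10% or fewer normal, the severe cut loses about 2 to 10 points. This stands for the severe cut only; the normal cut does worst there.

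**The calculation is not the planned model.** The SAP uses two visits, baseline cUS and random intercepts, and reports Holm-adjusted p-values. The figures are illustrative and do not measure what this trial would lose.

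**There are safeguards.** SAP 5.3 summarises all outcomes by arm, so the three-grade distribution can be shown. SAP 9 promises that all deviations will be listed in the report. Neither says which test of the grade counts.

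**Conclusion.** The point holds as a specification gap in one secondary outcome. The protocol classes it as ordinal; the SAP makes it binary with two alternative cuts, only partly settles the choice in 5.2.2, plans no ordinal analysis, and does not declare the change.

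Under the assumptions stated (50 per arm, one visit, unadjusted), leaving the choice open nearly doubles the false-positive rate for this outcome, from 5% to 9.3–9.9%. That is what would follow if whichever cut is significant were reported; nothing in the documents says that this is intended. At a common odds ratio of 2.5, dichotomising costs about 2 to 22 points of power at the severe cut and 7 to 43 at the normal cut.

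A reader might take one of these figures as the trial's maximum loss. The documents support neither a single figure nor a ceiling, since they give no grade distribution and no odds ratio. Other plausible inputs move the result both ways, and without proportional odds the severe cut can be the more powerful.

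The primary endpoint and its sample size are unaffected. This is a cheap improvement.

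**What to change.** Before the stage-1 analysis:

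1. In SAP 2.2.3 and 5.2.2, name one analysis of the grade: a cumulative-link mixed model on the three levels, with the fixed effects (treatment, baseline cUS, time) and random intercepts already planned.
2. Keep severe versus not severe as the single supportive binary analysis.
3. Remove normal versus moderate or severe as an alternative outcome. Its odds ratio may be shown beside that of the severe cut, solely to check proportional odds. That check needs both cuts; the severe cut alone cannot provide it.
4. Record the change in SAP 9.

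If the sponsor prefers a binary analysis, keep only the severe cut, so that 2.2.3 matches 5.2.2, and list the departure from the ordinal outcome type in SAP 9. This cures the open choice but not the loss of information.

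The cost is a few lines of SAP text and a different R function. No new data are needed. The downside of the ordinal model is its proportional-odds assumption.
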